### Data Collection, Management, and Confidentiality

Participants will be randomized 1:1 to the treatment and usual care groups via computer-generated sequence which will be concealed until after each patient’s enrollment. Given the nature of the study, blinding of caregivers and study coordinators to treatment groups is not feasible.

Data will be collected by study personnel in a manner consistent with patient confidentiality. For patients withdrawn from the study, no further data will be collected but existing study data to the point of withdrawal will be included in the final analysis which will be performed based on intention to treat.

All data obtained will be entered into REDCap (Research Electronic Data Capture), a secure electronic database that is password-protected and accessible only to the study team. Each participant will be assigned a unique identification code to protect their identity, and only the code will be used for forms, reports, and data analysis. Paper records containing protected health information will be maintained in locked file cabinets in a secure room accessible only to research personnel. All patient information will be kept confidential and managed according to the Health Insurance Portability and Accountability Act of 1996 requirements.

### Data Analysis

A per-protocol analysis will be used. Baseline characteristics of participants will be reported using percentages for categorical variables and mean with SD for continuous variables. Differences between the 2 treatment groups for the descriptive variables will be compared using chi-square tests for categorical variables and Kruskal-Wallis tests for continuous variables. The medications and dosages taken during the study will also be reported. The primary outcome of the CMAI-O score will be described at each of the 5 time points (baseline, day 1, day 2, day 3, and day 72 follow-up). A linear mixed effects model with time as a random effect will be used to analyze changes in the CMAI-O score over time. Both the unadjusted and an adjusted model with age, sex, and unit type as covariates will be reported. Age and sex were included as covariates as they are standard demographic factors that can influence behavioral outcomes. Unit type (medicine vs psychiatry) was included as it may impact patient management practices and potentially influence study outcomes. This model also allows for missing data which occurs in the dataset when a patient was discharged before the end of the study period. Secondary outcomes of ESAS-r and CGI scores will be analyzed in a comparable way with a linear mixed model. The end-of-study survey results will be described for each question. A per-protocol analysis will evaluate only the enrolled patients who followed protocol.

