### Objectives

The aim of this study is to investigate the effect of weighted blankets on aggression and agitation in hospitalized patients with dementia. We hypothesize that compared to controls, patients with agitation in the setting of dementia will show reduced agitation, reduced anxiety, and potentially improved sleep while hospitalized when provided with a weighted blanket.

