#### Intervention

Participants will be randomized 1:1 to either the usual care group or the weighted blanket group. The weighted blankets used are commercially available and purchased for the study. Patients randomized to the weighted blanket group will be provided with either a 10 lb, 15 lb, or 20 lb weighted blanket, ensuring that the weight is not more than 10% of the participant’s body weight. Participants will be withdrawn from the study if they refuse the blanket or are unable to tolerate it for more than 2 hours on the first night after enrollment. Participants can also be withdrawn from the study at any time if the primary team feels that further participation will jeopardize patient safety. Enrolled participants will use the blanket for a total of 3 consecutive nights, or until the time of discharge if that occurs sooner. Following participation in the study, participants will be allowed to keep the weighted blanket for future personal use. To reduce potential bias, the data analysis team will remain blinded to group assignment during statistical analyses, although investigators administering the questionnaires will not be blinded due to the nature of the intervention.

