#### Primary Outcome

The primary end point will be the change in CMAI-O over the course of the 3-night study period. The CMAI-O is a validated scale published in 2020 by Griffith et al [18] to quantify neuropsychiatric behavior in patients with dementia. Observers rank the frequency of 29 behaviors grouped into categories: physical aggressive behaviors (questions 1-11), physical nonaggressive behaviors (questions 12-21), verbal aggressive behaviors (questions 22-24), and verbal nonaggressive behaviors (questions 25-29). The frequency of each behavior is ranked as 1 (never), 2 (less than once per h), 3 (once per h), and 4 (several times per hour).

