#### Sample Size

We will target an enrollment of 30 participants in this pilot study. This sample size was chosen to balance the need for gathering preliminary data with the constraints of patient availability, time, and resources within our hospital setting. The sample size of 30 is sufficient to provide preliminary insights into the effects of weighted blankets on agitation, allowing us to explore trends and estimate effect sizes for future studies. Recruitment will be facilitated by daily review of hospital-wide behavior emergency response team activations and patient referrals from inpatient medicine and psychiatry primary services.

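### The primary CMAI-O model names time, not the patient, as its random effect and leaves the between-arm contrast unstated; fitted as written, it ignores within-patient correlation

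*Protocol article*

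**What the plan says.** The Primary Outcome section defines the end point: "The primary end point will be the change in CMAI-O over the course of the 3-night study period". Study Timeline and Follow-Up schedules the CMAI-O five times per patient: baseline, after each of three nights, and a final assessment. Under Objectives the question is comparative: "We hypothesize that compared to controls, patients with agitation in the setting of dementia will show reduced agitation".

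The Data Analysis section gives the primary model in one sentence: "A linear mixed effects model with time as a random effect will be used to analyze changes in the CMAI-O score over time". It then adds "Both the unadjusted and an adjusted model with age, sex, and unit type as covariates will be reported", with a reason for each covariate. It also says that the model accommodates data missing after early discharge, and that ESAS-r and CGI will be analysed in a comparable way with a linear mixed model. The section names no patient effect, no within-patient covariance and no between-arm contrast for the model.

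On size and allocation, the plan says "We will target an enrollment of 30 participants in this pilot study" and "Participants will be randomized 1:1 to either the usual care group or the weighted blanket group". The Sample Size section gives estimating effect sizes for future studies as one purpose.

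**The concern.** Ratings are correlated because they come from the same patient, so the patient is the grouping factor that the model needs. Time has five planned levels that are the same for everyone and belongs in the fixed part. A random effect of time alone lets all patients shift together at a given visit. It does not let one patient be persistently more agitated than another.

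Three things are at stake.

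- **Precision.** The uncertainty attached to the effect estimate would be wrong, and a usable effect size is one of the pilot's stated aims.
- **Estimand.** The sentence describes a course over time, whereas the objective is a difference from usual care. Patients must show agitation at entry, and "Recruitment will be facilitated by daily review of hospital-wide behavior emergency response team activations", so some fall in both arms is plausible. Only a between-arm contrast separates the blanket from that.
- **Missing visits.** A mixed model uses a discharged patient's earlier ratings to inform the missing ones only through the modelled within-patient correlation.

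**Working it through.** The plan states no alpha, power, SD or effect size, so there is no figure of its own to reproduce. The check asks what the stated model does to the standard error (SE) of a between-arm comparison.

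**Inputs from the protocol article.** 30 participants randomised 1:1, so n = 15 per arm if all are enrolled; m = 5 ratings per patient; primary end point is change over the three nights.

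**Assumptions, not in the document.** Complete data; equal variance σ² at each visit; equal correlation ρ between any two ratings of one patient, with ρ = 0.3, 0.5 and 0.7; two-sided 5% test; a group term added to the literal model so that a between-arm contrast exists. In balanced data a random time effect shared by all patients cancels from any between-arm difference, so the literal model treats the ratings as independent.

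**1. Between-arm difference in change, baseline to postnight 3**

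- True variance: 2 × 2σ²(1 − ρ)/n = 4σ²(1 − ρ)/n.
- Variance under the literal model: 4σ²/n.
- Model SE / true SE = 1/√(1 − ρ).
- Type I error = 2[1 − Φ(1.96/√(1 − ρ))].

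| ρ | SE too large by | Type I error, formula | Type I error, 20,000 simulations |
|---|---|---|---|
| 0.3 | 1/√0.7 = 1.20 | 1.91% | 2.0% |
| 0.5 | 1/√0.5 = 1.41 | 0.56% | 0.6% |
| 0.7 | 1/√0.3 = 1.83 | 0.03% | 0.09% |

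When patient-level change scores are compared instead, simulated type I error is 4.8% to 4.9%.

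At ρ = 0.5, in units of σ, the literal SE is √(4/15) = 0.516 and the true SE is √(2/15) = 0.365. For an assumed true difference in change of 1 SD, simulated power is 48% with the literal SE and 75% with patient-level change scores.

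**2. Between-arm difference averaged over the five visits**

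- True variance: 2σ²[1 + (m − 1)ρ]/(nm).
- Variance under the literal model: 2σ²/(nm).
- True SE / model SE = √(1 + 4ρ) = √2.2 = 1.48, √3.0 = 1.73 and √3.8 = 1.95.

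The error therefore runs in opposite directions for the two contrasts.

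**3. By-patient time slope without a patient intercept**

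Suppose the phrase means a random slope for each patient and nothing more. With baseline coded as time 0, such a model allows no persistent difference between patients at baseline. Simulating stable between-patient differences (visits at 0, 1, 2, 3 and 5.5 days, 500 runs per ρ), type I error for a between-arm difference in slope was 1.0%, 0.2% and 0%. The slope alone does not repair the SE. An intercept or an equivalent covariance is needed.

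**4. Model with no group term**

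Taken with only the terms listed, the model gives the pooled course. If the arms changed by −8 and −4 (illustrative), it would return their average, −6, and not the difference, −4.

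**The case against.** The strongest reply is that time as a random effect is often shorthand for a time trajectory within each patient. The remark about patients discharged early suggests that a patient-level longitudinal model was in mind. If it had a patient intercept as well as a slope, the SE need not be wrong and the missing-data statement could stand. This limits the point: the consequences above follow from fitting the sentence as written, not necessarily from what was intended. It does not rescue the sentence, which names a random effect and names the wrong one.

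A second reply is that an unlisted group term is only silence in a condensed article. That is largely right. The objective is comparative, the allocation is randomised, and analysts are to be blinded to group during the analysis, which would have little purpose unless the groups were compared.

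Three stronger readings are tempting, and the documents do not support them.

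- **A natural fall in agitation will be credited to the blanket.** Nowhere is within-arm change made the test, and a model without a group term pools the arms and credits neither. How far scores would fall unaided is also unknown. A rating of 2 on one aggression item suffices for entry, enrolment may occur at any point in the stay, and service referrals are a second recruitment source.
- **The trial faces a false-positive rate of 19% to 32%.** Simulation does give 18.5%, 26.1% and 31.6% for a group difference averaged over all five visits, but the plan never proposes that test. For the stated change end point the error is conservative.
- **The plan cannot estimate a blanket effect at all.** It leaves the contrast unstated, which is less than excluding it.

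**Conclusion.** The point holds as a misstatement in the primary analysis, not as an omitted detail. The random effect is attached to the wrong unit, and the model sentence does not name the between-arm contrast that the objective requires.

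If the model is fitted literally, the main cost for the stated end point is lost precision and power: an SE 20% to 83% too large over assumed correlations of 0.3 to 0.7. The statement about missing visits then also lacks its basis. The same wording carries over to ESAS-r and CGI.

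The sizes rest on 15 per arm, complete data and equal correlation between visits, and the document gives no correlation. If a by-patient slope with an intercept was intended, the numerical consequences need not arise and the correction is one of clarity. For a pilot meant to supply effect sizes, it should be settled before outcome data are compared by arm.

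**What to change.** Replace the model sentence with wording such as the following:

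*CMAI-O will be analysed with a linear mixed model with a patient random intercept (or a specified within-patient covariance) and fixed effects for visit and group. The primary estimate is the between-arm difference at postnight 3, with 95% confidence interval.*

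Then name one form of that estimate: the group-by-visit contrast for change from baseline to postnight 3, or a baseline-adjusted group effect at postnight 3. Either answers the question, and one should be chosen in advance. If a by-patient time slope is wanted, say so and keep the patient intercept or an equivalent covariance beside it.

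Use the same form for ESAS-r and CGI, and state that within-arm change is descriptive. The degrees-of-freedom method can be left to the trial statistician.

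The cost is wording only: no change to data collection, visits or sample size. The article reports 24 enrolled by November 2024 and data collection expected to finish by March 2026. It does not say whether any outcome data have been analysed, so the amendment should be dated and should record that status.

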#### Study Population and Recruitment

Patients will be recruited from a single large tertiary care hospital. Participants are eligible for inclusion if they are 60 years or older, have a documented clinical diagnosis of dementia, and are currently admitted to either a medicine or psychiatry primary service. All participants are required to have ongoing agitated behaviors at the time of enrollment as demonstrated by an elevated CMAI-O with a score of 2, 3, or 4 on at least one aggression-related item (items 1-11 or 22-24) [18]. Patients will be excluded if they have severe pain likely to be exacerbated by the use of the weighted blanket, have significant burns or wounds for which weighted blanket use could potentially be detrimental, or are admitted on a 72-hour involuntary hold. Participants can be enrolled at any point during their hospitalization. Hospitalizations will not be prolonged for the purpose of the study. To reflect real-world conditions, all other usual medical care will be continued at the discretion of the primary medical or psychiatric team.

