#### Study Timeline and Follow-Up

Identical study assessments will be completed by the patient’s caregiver (either registered nurse or patient care assistant) for both the usual care group and the weighted blanket study group. Cohen-Mansfield Agitation Inventory (CMAI-O), ESAS-r, and CGI scores will be collected at 5 study time points (baseline, postnight 1, postnight 2, postnight 3, and a final assessment 48-72 hours after the last use of the weighted blanket). A total of 3 nights were determined to be sufficient for assessing trends in agitation, anxiety, and sleep, while also testing the feasibility of the intervention in a real-world clinical environment. Within 2-4 weeks following hospital discharge, study coordinators will contact the patient’s legally authorized representative (LAR) to assess for continued use of the blanket. Refer to the patient timeline (Table 1).

**Table 1 table1:** Patient timeline.

Assessment	Baseline (enrollment)	WB^a^ day 1	WB day 2	WB day 3	Final within 72 hours of last use of WB (cohort 1) or no WB (cohort 2)	Within 2-4 weeks post discharge
CMAI-O^b^	✓	✓	✓	✓	✓	
ESAS-r^c^	✓	✓	✓	✓	✓	
CGI^d^	✓	✓	✓	✓	✓	
Posthospitalization phone call to assess continued weighted blanket use						✓

^a^WB: weighted blanket.

^b^CMAI-O: Cohen-Mansfield Agitation Inventory.

^c^ESAS-r: Edmonton Symptom Assessment System Revised.

^d^CGI: Clinical Global Impression.

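### The adjusted CMAI-O model lists age, sex and unit type but neither baseline CMAI-O nor a common baseline mean; unless one of these is used, a 30-patient trial loses precision

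*Protocol article*

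**What the plan says.** The Primary Outcome section defines a change endpoint: "The primary end point will be the change in CMAI-O over the course of the 3-night study period". Study Timeline and Follow-Up schedules CMAI-O, ESAS-r and CGI together: "scores will be collected at 5 study time points (baseline, postnight 1, postnight 2, postnight 3, and a final assessment". A baseline CMAI-O is also needed to enter the trial, since Study Population and Recruitment requires ongoing agitation "as demonstrated by an elevated CMAI-O with a score of 2, 3, or 4 on at least one aggression-related item".

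Data Analysis plans a linear mixed model of CMAI-O change over time, with time as a random effect. On covariates it says: "Both the unadjusted and an adjusted model with age, sex, and unit type as covariates will be reported". It gives a reason for age and sex (usual demographic influences on behaviour) and for unit type (differences in patient management). Baseline CMAI-O is not listed. The section does not say whether the baseline score is part of the modelled response or, if it is, whether the two arms share a baseline mean. Neither the unadjusted nor the adjusted model is named as primary. ESAS-r and CGI are to be analysed in a comparable way.

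**The concern.** The covariate list is a stated and justified choice, so this is more than a detail passed over in a condensed article. The three chosen variables are generic. The patient's own score on the same scale at enrolment, which is likely to be prognostic, is left out. For a change endpoint, the handling of baseline largely determines how precise the treatment contrast is.

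The sample size was set by feasibility, and the trial's purpose is to give preliminary effect estimates for later studies. Precision is therefore the main product, and it cannot be bought with more patients. In groups of about 15, a chance difference in baseline agitation is also likely. An estimate that does not adjust for baseline carries part of that difference. Two models with no order of priority leave the later study with two candidate effect sizes.

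**Working it through.** **Inputs from the protocol article.** Total sample: "We will target an enrollment of 30 participants in this pilot study". Allocation: "Participants will be randomized 1:1 to either the usual care group or the weighted blanket group", so n = 15 per arm. Basis of the sample size: "This sample size was chosen to balance the need for gathering preliminary data with the constraints of patient availability, time, and resources". No alpha, power, SD, target effect or correlation is stated, so there is no figure of the plan's own to reproduce.

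**Assumptions.** Equal SDs at all visits, one common correlation ρ between any two visits (0.3, 0.5, 0.7), complete data, two-sided alpha 0.05. Variances are in units of SD² and omit the common factor 2/n.

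**Single post-baseline visit.**
- Baseline-adjusted: 1 − ρ² = 0.91, 0.75, 0.51.
- Baseline as a response with separate arm means (equivalent to a change score): 2(1 − ρ) = 1.40, 1.00, 0.60. The ratio to adjusted is 2(1 − ρ)/(1 − ρ²) = 2/(1 + ρ) = 1.54, 1.33, 1.18.
- Post-baseline score only, no baseline term: 1. The ratio is 1/(1 − ρ²) = 1.10, 1.33, 1.96.

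To match a baseline-adjusted analysis of 30 patients, the change analysis would need 30 × 1.54 ≈ 46, 30 × 1.33 ≈ 40 or 30 × 1.18 ≈ 35 patients.

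**Mean of the three post-night scores.**
- Baseline-adjusted: (1 + 2ρ)/3 − ρ² = 0.443, 0.417, 0.310.
- Separate arm means: 4(1 − ρ)/3 = 0.933, 0.667, 0.400. Ratios 2.11, 1.60, 1.29.
- Post-baseline only: (1 + 2ρ)/3 = 0.533, 0.667, 0.800. Ratios 1.20, 1.60, 2.58.
- Baseline as a response with a common mean in both arms: generalised least squares gives 0.443, 0.417, 0.310, the same as baseline-adjusted. There is no loss.

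**Illustrative power, single visit, true difference 0.8 SD (assumed).** By the normal approximation, power is Φ(0.8/√(2v/15) − 1.96), where v is the variance factor. At ρ = 0.5 the change score (v = 1.00) gives 0.59 and the adjusted contrast (v = 0.75) gives 0.72. Allowing for one estimated covariate, v = 0.75 × (1 + 1/26) gives 0.70. A simulation of 8,000 trials gives 0.56 and 0.68. At ρ = 0.7 the normal approximation gives 0.81 and 0.87.

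**Chance imbalance.** The baseline difference between arms has standard deviation √(2/15) = 0.37 SD. It exceeds 0.3 SD in about 41% of such trials and 0.5 SD in about 17%. Given a baseline gap g, a change contrast is shifted by (1 − ρ)g in size and a post-only contrast by ρg. At ρ = 0.5 and g = 0.5 SD, both are 0.25 SD.

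**The case against.** The strongest reply is that the article does not show that any precision is lost. The sentence in Data Analysis that lists five time points concerns description, and the model sentence does not define the response or the fixed effects. If baseline is a repeated response, one would not expect it among the covariates as well, and with a common baseline mean the loss is zero. The full protocol or analysis plan, not shown here, may settle this. This reply stands as far as it goes: the loss is conditional. It does not remove the point, because the article fixes and justifies a covariate set, states no common baseline mean, and loses precision under both other model forms.

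A reader might infer several stronger things, and the documents support none of them:
- That baseline CMAI-O is the strongest predictor. No correlation, SD or ranking of predictors is given, and the eligibility rule may narrow the baseline range and lower the correlation.
- That the plan definitely compares raw changes. This is a plausible inference from the list of time points, but it is not stated.
- That the estimate is biased, or that regression to the mean from selecting agitated patients favours one arm. Allocation is randomised and concealed, and such regression affects both arms alike in expectation. Only a chance gap matters, and its effect is already counted in the sampling variance.
- That the trial misses its power. It states none.

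It is also fair to say that both models are to be reported, so the text does not allow only the more favourable one to be shown. What is missing is which of them is the main one.

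**Conclusion.** The point holds as a conditional loss of precision. The stated covariate set omits baseline CMAI-O and no common baseline mean is specified. Unless one of these is used, the single-visit variance is inflated by 18% to 54% if baseline is a response with separate arm means, and by 10% to 96% if baseline is left out altogether, over correlations of 0.3 to 0.7. For the three-night mean the inflation is 29% to 111% and 20% to 158% respectively. With a common baseline mean it is zero.

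These figures rest on assumed correlations, a common correlation between visits, and complete data for 15 patients per arm. Early discharge and withdrawal, which the article expects, would reduce the information further. The power figures are illustrations at an assumed effect and do not contradict anything the article claims. The comparison remains unbiased in expectation. The improvement is worth making because it is nearly free and the sample size is capped by feasibility.

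**What to change.** Name one primary model for CMAI-O, in one of two forms:
- post-baseline CMAI-O as the response, with baseline CMAI-O, age, sex and unit type as covariates; or
- baseline kept in the response vector with a common mean in both arms, plus age, sex and unit type.

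Use one form only, since a baseline that is both a covariate and a response is used twice. Keep the unadjusted model as supportive. Handle ESAS-r and CGI severity in the same way, each with its own baseline.

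The cost is about one degree of freedom and a change of analysis wording. No new data are needed, because the baseline scores are already scheduled for every patient. The article expects data collection to finish by March 2026 and keeps the analysis team blinded to allocation, so the choice should be recorded before any comparison by arm is run.

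### The protocol article fixes both intention to treat and per-protocol as the analysis, labels neither as primary, and has a blanket-only withdrawal rule that makes the choice matter

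*Protocol article*

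**What the plan says.** Two sections of the protocol article name the analysis population.

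- **Data Collection, Management, and Confidentiality:** for withdrawn patients, "existing study data to the point of withdrawal will be included in the final analysis which will be performed based on intention to treat".
- **Data Analysis, first sentence:** "A per-protocol analysis will be used".
- **Data Analysis, last sentence:** "A per-protocol analysis will evaluate only the enrolled patients who followed protocol".

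Data Analysis never mentions intention to treat, and no section ranks the two analyses. The article gives no criteria for having followed protocol.

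Three further statements decide who is affected:

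- **Intervention, tolerance rule:** "Participants will be withdrawn from the study if they refuse the blanket or are unable to tolerate it for more than 2 hours", applied on the first night.
- **Intervention, safety rule:** "Participants can also be withdrawn from the study at any time if the primary team feels that further participation will jeopardize patient safety".
- **Data Collection, Management, and Confidentiality:** "For patients withdrawn from the study, no further data will be collected".

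The primary endpoint is change in CMAI-O over the three nights. Allocation is 1:1, and "We will target an enrollment of 30 participants in this pilot study".

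**The concern.** A blanket patient who is withdrawn on night 1 belongs in the final analysis under one section and, on the natural reading, is left out under the other. Both statements cannot govern the primary result. With both in place, the population could be settled after the data are seen.

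The two populations also differ in a way tied to the arm. Only someone given a blanket can refuse it or fail to tolerate it. The safety rule can remove patients from either arm, but usual-care patients have little protocol to breach. A per-protocol comparison would therefore set a selected blanket arm against a nearly unselected control arm.

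The Sample Size section says the pilot is meant to estimate effect sizes for later studies, so a selection effect in the estimate would carry into their planning.

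**Working it through.** **1. The contradiction.** This needs no arithmetic. Take a blanket patient withdrawn on night 1.

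| Section | Status of that patient |
|---|---|
| Data Collection, Management, and Confidentiality | Included, with data up to withdrawal |
| Data Analysis | Excluded, if withdrawal means protocol was not followed |

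The last sentence of Data Analysis, read alone, could describe an added analysis. The first sentence of that section names per-protocol as the analysis, without qualification.

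**2. Size of the bias.** The article has no figure to reproduce, because the target of 30 rests on feasibility. What follows is an illustration.

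Input from the article: 30 patients at 1:1, so n = 30/2 = 15 per arm.

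Assumptions, none of them in the article:
- no true effect;
- k = 2 to 4 blanket patients excluded and no controls;
- the excluded patients are those with the highest intolerance, which correlates ρ = 0.3 to 0.7 with agitation;
- baseline and follow-up scores have equal SD and correlation r = 0.5.

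The SD of change is √(2(1 − r)) = 1 score SD, so one unit serves for both. Negative values favour the blanket.

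Let m be the amount by which mean intolerance falls among the retained blanket patients. The four largest of 15 standard normal values have expected values 1.737, 1.248, 0.947 and 0.714.
- k = 2: m = (1.737 + 1.248)/13 = 0.230
- k = 3: m = (1.737 + 1.248 + 0.947)/12 = 0.328
- k = 4: m = (1.737 + 1.248 + 0.947 + 0.714)/11 = 0.422

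*Per-protocol, intolerance driven by baseline agitation.* Removing the most agitated patients removes those who would regress most. Bias in change = +(1 − r)ρm.
- Smallest: 0.5 × 0.3 × 0.230 = +0.03 SD
- Largest: 0.5 × 0.7 × 0.422 = +0.15 SD, against the blanket

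*Per-protocol, intolerance driven by later agitation.* Bias in change = −(1 − r)ρm.
- From about −0.03 to −0.15 SD, toward the blanket

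**3. Does naming all randomized patients remove the bias?** Under the current rules a first-night withdrawal supplies a baseline score and little or nothing after it. The check used a likelihood analysis with all baselines and whatever follow-up exists.
- Baseline-driven: bias 0, because the observed baseline accounts for the missing follow-up.
- Driven by later agitation: bias ≈ −(1 − r²)ρm. Smallest: 0.75 × 0.3 × 0.230 = −0.05 SD. Largest: 0.75 × 0.7 × 0.422 = −0.22 SD.

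A simulation of the same two-time-point set-up gave per-protocol bias of +0.03 to +0.15 SD and about −0.04 to −0.15 SD. For the available-data analysis it gave zero, and about −0.05 to −0.24 SD.

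**4. Scale.** With 15 per arm the standard error of a difference is √(2/15) = 0.37 SD. A bias of 0.15 SD is therefore about 0.15/0.37 = 0.4 standard errors.

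**The case against.** The strongest reply has four parts.

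- **This is a small pilot, and population definitions are often left to an analysis plan.** That excuses missing detail, such as the adherence criteria. It does not excuse two opposed statements about which analysis is done. A reader with only the article cannot tell which one an analysis plan would follow.
- **Exclusions need not be one-sided.** Safety withdrawals apply to both arms, and with no definition of following protocol, missed assessments could count in either. This stands in part. The right claim is that exclusions fall mainly on the blanket arm, because one named route is open only there.
- **The direction is not shown.** A reader might infer that per-protocol flatters the blanket and inflates false-positive findings. The article does not support that. Nothing in it links refusal or intolerance to worse agitation; with no such link there is no bias. For a change score the sign can go either way. The article also states no significance level, so there is no error rate to inflate. This part stands in full.
- **Intention-to-treat wording is not a cure.** This also stands. If intolerance follows later agitation, the residual bias is no smaller than under per-protocol, because data collection ends at withdrawal.

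A reader might also infer that per-protocol exclusions would unblind the analysts. Nothing says the analysts assign adherence. Baseline-only records from early withdrawals would be just as visible under intention to treat.

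**Conclusion.** The contradiction is established from the text alone and leaves the primary analysis population undetermined. It should be resolved before analysis.

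Per-protocol exclusions would weigh mainly on the blanket arm, so that analysis would no longer be a randomized comparison and can bias the CMAI-O change. Under the stated assumptions the bias is roughly −0.15 to +0.15 SD. That is modest beside the sampling error of a 30-patient trial, and its sign is unknown. The figures are for scale only: exclusion counts and correlations are assumed, and two time points stand in for the five-assessment mixed model.

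Making all randomized patients primary restores the randomized comparison as the target. It does not remove all bias while follow-up ends at withdrawal.

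**What to change.** 1. In Data Analysis, replace "A per-protocol analysis will be used" with one primary analysis: all randomized patients in the arm assigned, using every available assessment in the mixed model, with baseline included.
2. Keep per-protocol only as a labelled sensitivity analysis, with adherence criteria written down before the data are seen.
3. Reconcile Intervention, Data Collection and Data Analysis on what happens after withdrawal. Either the already scheduled CMAI-O assessments continue after blanket use stops, where consent allows, or the article states that the primary result assumes data are missing at random for early withdrawals and adds a sensitivity analysis for it. Data Analysis at present discusses missing data only for early discharge. This concerns data collection; no view is taken on the tolerance rule.

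The Results section reports 24 of 30 patients enrolled by November 2024. Continued assessment can therefore help at most the remaining 30 − 24 = 6, plus any patient then still under assessment. The missing-at-random statement and its sensitivity analysis are likely to be needed in any case.

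**Cost:** an amendment to the wording, a few more routine assessments, one added sensitivity analysis, and an estimate that may be less favourable to the blanket.
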